### Data collection

Due to summative and formative evaluations, different types of data will be collected in this study. Self-reported outcomes will be surveyed via online questionnaires at all measurement time points (t0, t1, t2, t3). Users withdrawing their participation in the study or the health program prematurely, will receive a short logoff questionnaire upon deregistration to assess reasons for study termination. Usage behavior data will be stored from all participants who log onto their health program, from their first to their last login. Qualitative data will be collected during telephone interviews with participants in the intervention group in the *Smoking Cessation* RCT.

Sports and nutritional medical data will be collected by the IfSS as part of the two substudies. Physiological outcomes will be evaluated in each via four medical examinations (t0, t1, t2, t3). Completing the online questionnaire is a precondition for participating in one of the medical substudies. Detailed information on this data collection will be published in a separate study protocol.

### Quantitative data

#### Online questionnaires: baseline (t0) and catamnesis (t1–t3)

Online questionnaires specifically designed for each health goal are applied in all RCTs to survey socio-demographic, health-related, and psychological variables.

The variables and constructs of the online questionnaire surveys of all RCTs at the four measurement time points are shown in Tables 2, 3, and 4. We used validated instruments whenever possible. The wording in some instruments has been modified and other questions newly developed by the research team. A new questionnaire to investigate eating behavior [21] has been developed as part of the medical preliminary study (details see separate study protocol of the medical substudies [22].

**Table 2 Tab2:** Variables of three health goal-specific questionnaires: sociodemographic and baseline variables

Variables/constructs	Source/origin/analyses	Health goal /RCT	Number of items	Time measure points			
				t0	t1	t2	t3
**Sociodemography**							
Age	Self-developed/means in years	W, F, S	1	**x**	**x**	**x**	**x**
Gender	Self-developed/percentages	W, F, S	1	**x**	**x**	**x**	**x**
Postal code (2 digits)	Self-developed /percentages	W, F, S	1	**x**	**x**	**x**	**x**
Characteristic of residence (big city to rural)	Self-developed/percentages	W, F, S	1	**x**	**x**	**x**	**x**
Native language	Migration status; adapted [47]/percentages	W, F, S	2	**x**			
Nationality	Self-developed/percentages	W, F, S	1	**x**			
Marital status	Indicators of rehabilitation status (IRES) [48]/percentages	W, F, S	1	**x**			
Persons in the household	IRES [48]/means	W, F, S	2	**x**			
Highest school degree	IRES [48]/percentages	W, F, S	1	**x**			
Highest professional qualification	Questionnaire for Health-Related Resource Use in an Elderly Population FIMA [49]/percentages	W, F, S	1	**x**			
Employment	Indicators of rehabilitation status (IRES); adaped [48]/percentages	W, F, S	2	**x**	**x**	**x**	**x**
Net income	IRES; adaped [48]/percentages of categories	W, F, S	1	**x**			
Working hours	IRE S[48] and one self-developed item/means	W, F, S	2	**x**	**x**	**x**	**x**
**Basic variables**							
Membership in health insurance	Self-developed/percentages	W, F, S	1	**x**			
Knowledge of the study	Self-developed/percentages	W, F, S	1	**x**			
Experience with online health programs	Self-developed/means and percentages	W, F, S	1	**x**			
Current use of (other) online health programs	Self-developed/percentages	W,F,S	6	**x**	**x** (6)	**x**(6)	**x** (6)
Further internet use in general and regarding health subjects	Self-developed/percentages	W, F, S	10	**x**	**x** (1)	**x** (1)	**x**(1)
Previous attempt at behavior change	“Berlin Risk Appraisal and Health Motivation Study” (BRAHMS [50]); adapted to specific health goal/means	W, F, S	2 4	**x**			
Actual health behavior	Self-developed/percentages	W, F, S	1	**x**	**x**	**x**	**x**
Height	IRES [48] (Use for calculation of Body mass index)	W, F, S	1	**x**			
Smoking	Self-developed/percentages	W, F	1	**x**			

Health goals: W=”Losing and Maintaining Weight”; F=”Increasing Fitness”, S=” Smoking Cessation”;

measurement time point: t0 = Baseline, t1 = first follow-up; t2 = second follow-up; t3 = third follow-up; IRES = Indicators of rehabilitation status

**Table 3 Tab3:** Variables of three health goal-specific questionnaires: primary outcomes and secondary outcomes

Variables/Constructs	Source/Origin/Analyses	Health goal	Number of items	Time measure points			
				t0	t1	t2	t3
**Primary**^**i**^**and secondary**^**ii**^**Outcomes**							
Weight	IRES [48]/Changes in mean kilogram	**W**^**i**^,F^**ii**^,S^ii^	1	**x**	**x**	**x**	**x**
Physical activity	Physical Activity and Sport Activity Questionnaire (BSA-F 3.0) [51]/Changes in mean score	W^ii^,**F**^**i**^	17	**x**	**x**	**x**	**x**
Smoking abstinence in the last 30 days	Self –developed/Changes in percentages (dichotomous data)	**S**^**i**^	1	**x**	**x**	**x**	**x**
Health related goal intention	Goal intention [52] [53]; adapted/Differences of mean values	W^ii^,F^**ii**^,S^ii^	1	**x**	**x**	**x**	**x**
Sport- and movement-related self-concordance	Sport- and movement-related self-concordance [54]/Changes in mean score	F^ii^	12	**x**	**x**	**x**	**x**
Self-efficacy (dietary)	Testing phase-specific self-efficacy [55]/Changes in mean score	W^ii^	7	**x**	**x**	**x**	**x**
Self-efficacy (smoking)	Scales for the measurement of self-efficacy and decisional balance in the process of behavioral change in smokers [56]/Changes in mean score	S^ii^	9	**x**	**x**	**x**	**x**
Barrier management in physical exercise	Barriers and barrier management in physical exercise [57]/Changes in mean score	F^ii^	29	**x**	**x**	**x**	**x**
Expectation of consequences	BRAHMS [50]; adapted/Changes in mean score	W^ii^, S^ii^	18	**x**	**x**	**x**	**x**
Action planning	Action plans and coping plans for physical exercise [58]/Changes in means score	F^ii^	13	**x**	**x**	**x**	**x**
Risk perception	Risk perceptions of cigarettes and e-cigarettes [59]; adapted/Changes in mean score	S^ii^	5	**x**			
Perceived goal attainment	Self-developed/Differences in means	W^ii^,F^ii^,S^ii^	2		**x**	**x**	**x**
Eating behavior German Eating Behavior Scale	German Eating Behavior Scale (SEV)*;article submitted [21]/Changes in mean score	W^ii^, F^ii^	32	**x**	**x**	**x**	**x**
Nicotine dependence	Fagerstrom Tolerance Questionnaire *(*FTND [60])/Changes in mean score	S^ii^	6	**x**	**x**	**x**	**x**
Health-related quality of life	Short Form 12 Health Survey (SF-12) [61]/Changes in mean score	W^ii^,F^ii^,S^ii^	12	**x**	**x**	**x**	**x**

Health goals: W=”Losing and Maintaining Weight”; F=”Increasing Fitness”, S=” Smoking Cessation”

Measurement time point: t0 = baseline, t1 = first follow-up; t2 = second follow-up; t3 = third follow-up; IRES = indicators of rehabilitation status

Primary outcome of the related health goals; highlighted in bold

Secondary outcomes of the related health goals

^*^This instrument (SEV) was developed in the preliminary study [22]

**Table 4 Tab4:** Variables of three health-specific questionnaires: confounder, use, evaluation, and cancelation of the programs

Variables/constructs	Source/origin/consideration in analyses	Health goal	Number of items	Time measure points			
				t0	t1	t2	t3
**Confounder**							
Mental illness	Patient Health Questionnaire (PHQ-2 [62])/mean score One self-developed item/dichotomous	W, F, S	3	**x**	**x**	**x**	**x**
Health impairments	Comorbidity Score (KoMo) [32]/mean score	W, F, S	24	**x**			
General state of health	BRAHMS [50]; adapted	W, F, S	1	**x**			
Addictive substances other than tobacco (s)	Alcohol, Smoking and Substance Involvement Screening Test (WHO-ASSIST), question N°2 [63] ; three of ten items: alcohol, cannabis, sedatives and sleeping pills/value of each Item	S	3	**x**	**x**	**x**	**x**
Social support	The weigh-related interactions Scale (WRIS) [26]; adapted/mean score	W	14	**x**	**x**	**x**	**x**
	Social support [64] (in prep.)/mean score	F	12	**x**	**x**	**x**	**x**
	Partner Interaction Questionnaire (PIQ-20 [65]); adapted/mean score	S	17	**x**	**x**	**x**	**x**
**Evaluation of the program***							
Use and evaluation of the online programs*	Self-developed/mean duration of use in weeks and mean score of evaluation	W, F, S	19		**x**	**(x*)**	**(x*)**
Recommendation of the online program	Self-developed/percentages of three levels	W, F, S	1			**x**	**x**
Premature program- and/or study termination**	Self-developed/percentages of different reasons	W, F, S	5	**(x)**			
Text box for additional comments	Self-developed/categorizations and subsequent description of percentages	W, F, S	1	**x**	**x**	**x**	**x**

Health goals: W=”Losing and Maintaining Weight”; F=”Increasing Fitness”, S = “Smoking Cessation”

Measurement time point: t0 = baseline, t1 = first follow-up; t2 = second follow-up; t3 = third follow-up

*****These questions are queried only once. If t1- or t2-questionnaire are not filled out by users, these questions are displayed again in the following measurement time point

******Users withdrawing participation in the study or their health program prematurely receive a logoff questionnaire upon deregistration with up to 5 items concerning the reasons for quitting the program and/or study. Additionally, it contains the same questions regarding their usage and evaluation of the program like participants in the t1 online questionnaires. The programming of the questionnaires and databases ensures that participants can only fill in these questions once

Before the online implementation, we pretested the questionnaires for understandability and usability by applying a “think-aloud method” with 11 participants (see supplement 2). Additionally, four of our research team members tested the questionnaires in advance through an expert review. During the process of online implementation and technical realization, two members of the research team monitored the rigorous implementation and web-based display of the questionnaires.

#### Usage behavior data

Usage behavior data will be collected from all participants engaged in the web-based health programs (intervention- and control groups) from their first to their last login. These data are partially collected at the participant level (frequencies and duration of program logins, logged activities [only intervention group]), and partially aggregated (page views).

### Qualitative data

Participants in the *SmokingCessationCoaching* (only participants in the intervention group of the corresponding RCT) will be invited to participate in a telephone interview after completing the t1-questionnaire. The duration of each interview will be 30–45 min.

Program compliance, usage intensity, motivation, and user satisfaction as well as smoking history and sociodemographic data will be surveyed by SEVERA-team researchers posing the following key questions.

*The pretested interview guideline includes the following key questions:*
What experiences did you have with the smoking cessation program?How did you feel in the smoking cessation preparation phase?How was your first day not smoking?From your point of view, how was the program’s usability?Did you take advantage of the personal telephone counseling offered in the *SmokingCessationCoaching*? If so, can you tell me about your experiences? If not, why did you not engage with the telephone counseling?What motivated you to begin this non-smoking program (also in comparison to other programs)?How satisfied were you with this non-smoking program and why?Would you recommend this smoking cessation program to others? If so, why would you recommend it, and if not, why would you not recommend it to others?Sociodemographic data: age, gender, native language, graduation, professional qualification, employment, and experience with computer-aided programs.Smoking history
Are you currently a smoker?
i.If no: How long have you not smoked a cigarette?ii.If no: How confident are you that you will manage to keep from smoking and why?iii.If yes: What are the reasons that you currently smoke?iv.If yes: Would you like to go through the program again, or where would you prefer to start?How long did you smoke?How many cigarettes a day did/do you smoke?When did/do you smoke your first cigarette in the morning?Have you tried to quit smoking before? (If so, how often? How successfully?)Had you participated in any other smoking cessation programs before this online program? (If so, which?)Have you used nicotine-replacement products as a cigarette alternative? (If so, which ones?)

### Data management

All quantitative research data are recorded and stored with individual pseudonyms by Vilua Healthcare GmbH (https://vilua.com/services/). Vilua has years of experience managing large datasets related to health programs and research projects and applies high quality standards in terms of data protection and data management.

Since the study started, Vilua sends at regular 2-day intervals datasets to SEVERA which include the number of received baseline-questionnaires in each health goal, randomized users of the programs, as the well as the number of questionnaires of all the following assessment time points distributed, received, and blocked due to exceeding the response time (eight weeks maximum). Due to this monitoring process, the research teams and Vilua are reviewing whether online recruitment and e-mailing of the questionnaires are technically successful. Users are able to contact Vilua the SEVERA and/or IfSS to address technical problems. Possible irregularities are immediately clarified between Vilua and scientific staff members of SEVERA and existing problems (e.g., failures in the storage of usage behavior data, feedback from users about technical errors, etc.) are logged by Vilua, SEVERA, and the IfSS.

*The TK health insurance fund will have no access to this study’s raw data*, *but is only informed about the progress. There exist no competing interests*.

In addition, SEVERA regularly prepares monitoring reports and communicates them to all the collaboration partners. The reports support the decision-making process, shared by the entire project team, to strengthen recruitment efforts and, finally, to complete the recruitment.

Data from the questionnaires are assessed approximately every 14 to 30 days for control purposes. Usage behavior data from the program are transferred at larger intervals. The data transfers are carried out by Vilua via a secure cloud of the Medical Center – University of Freiburg. The data are conducted via comma-separated values (csv) format and merged into the statistic program *Statistical Package for the Social Sciences* (SPSS) data files (IBM SPSS; Version 26), *R* (Version 4.0.3), and *IDE R Studio* (Version 1.2.5033).

After plausibility checks conducted by the scientific staff members of SEVERA, data analyses will be performed by SEVERA and IfSS.

The telephone interviews will be stored digitally as audio files and analyzed by scientific staff of SEVERA. Due to data protection requirements, parts of the interviews including personal information on the participants will be deleted by research assistants. A separate ID will be used to pseudonymize the interviews. The transcriptions of the audio recordings will be conducted by an external office. The data will be transferred via the secured connection to the file server provided by this office. To carry out the qualitative data analysis (QDA), the software MAXQDA (Version2020) will be used.

The *TK health insurance fund* will have no access to this study’s raw data but is only informed about the recruitment progress.

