### Research questions and hypothesis

The following questions and hypotheses are being investigated in this study
What effects do the online programs within the three health goals *Losing and Maintaining Weight*, *Increasing Fitness*, and *Smoking Cessation* have on the primary and secondary outcomes variables reported by participants?We assume that we will observe statistically significant improvements with small to medium effect sizes for each program.Will the intervention groups (interactive health programs) in each RCT reveal stronger effects on primary and secondary outcomes in comparison to the control groups (non-interactive health programs)? We will test the hypothesis that the intervention groups’ changes in the primary and secondary outcomes are more positive than the control groups’. Our focus is on long-term effects so we will analyze the change between baseline (t0) and 1 year after the intervention finishes (t3), while short-term effects are part of the secondary analyses. We expect small to medium effect sizes from the comparison between these two groups.Does the intensity of use of health programs have an impact on their effects?The hypothesis we test is that study participants who use their health program more frequently and intensively achieve better outcomes than study participants who use the program less often or less intensively.How satisfied with the programs offered are the study participants in the intervention- and control groups? This question will be examined exploratively in secondary analyses.

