### Sample size calculation

#### Randomized controlled trials

We calculated the sample size for each randomized controlled trial (RCT) separately (see Table 5) by considering the effect sizes of the primary outcomes in comparable trials [8–11], the α-error (0.05), and the power we were striving for (1 − *β* = 0.80). Our power analyses were done using GPOWER software. While we assumed a general online-RCT dropout rate of 50% [45, 46], we estimate a dropout rate of about 15% in the medical substudies in light of experiences with similar studies involving personal medical examinations. We have accounted for an additional 10% buffer for the online RCTs.

**Table 5 Tab5:** Sample size calculations for the three RCTs including medical substudies

Health goals	“Increasing Fitness“		“Losing and Maintaining Weight”		“Smoking Cessation“
RCTs	Online questionnaire study	Online-questionnaire study + medical substudy:	Online questionnaire study	Online-questionnaire study + medical substudy:	Online questionnaire study
**Primary outcome**	Physical activity (BSA)	questionnaire study: physical activity (BSA); medical examinations: VO_2 max_	Weight loss	Questionnaire study + medical examinations: weight loss	Abstinence from smoking
**Effect assumption for primary outcome**	effect size = 0.25	questionnaire study: effect size = 0.25 ; medical examinations: effect size = 0.45	Effect size = 0.50	Effect size = 0.50	15% in intervention group versus 2% in control group
**Required case-number results** (two-sided, alpha = 0.05, beta = 0.80)	253 (for each intervention group IG and control group CG)^1^	79 (for each IG and CG)^2^	253 (for each IG and CG)^1,3^	64 (for each IG and CG)^2^	77 (for each IG and CG)
**(assumed dropout)** **minimally required sample size**	(50%) 506 (for each IG and CG)	(15%) 93 (for each IG and CG)	(50%) 506 (for each IG and CG)	(15%) 75 (for each IG and CG)	(50%) 154 (for each IG and CG)
**total sample size (IG + CG + ca. 10% buffer for questionnaire study**	(506 + 506) × 1.1 *N* = 1.114	(93 + 93) *N* = 186	(506 + 506) × 1.1 *N* = 1.114	(75 + 75) *N* = 150	(154 + 154) × 1.1 *N* = 339

IG = intervention group (specific online coach for the health goal chosen), CG = control group (specific health information for the health goal chosen)

^1^As we aimed to assess the groups undergoing additional medical exams separately from those only completing the online questionnaire, the former group’s sample size is not included in this calculation

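### The t3 primary outcome is obtained only through a returned questionnaire of about 91 to 152 items that closes after eight weeks; a short primary-outcome form for late non-responders would reduce reliance on imputation

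*Protocol article*

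**What the plan says.** - **Route.** Under Data collection: "Self-reported outcomes will be surveyed via online questionnaires at all measurement time points". No other route to the online RCTs' primary outcomes is described.
- **Window.** Under Data management, the monitoring data count follow-up questionnaires that were sent, received, or "blocked due to exceeding the response time (eight weeks maximum").
- **Primary outcomes (Table 3).** Weight has one item ("IRES [48]/Changes in mean kilogram"), Smoking has one item ("Smoking abstinence in the last 30 days"), and Fitness has 17 items ("Physical Activity and Sport Activity Questionnaire (BSA-F 3.0) [51]/Changes in mean score").
- **Time point.** Under Research questions and hypothesis, the focus is long-term: "we will analyze the change between baseline (t0) and 1 year after the intervention finishes (t3").
- **Expected loss.** Under Sample size calculation: "While we assumed a general online-RCT dropout rate of 50% [45, 46"]. Trial status adds that loss could be higher.
- **People who stop.** Those who deregister get a logoff form on reasons, use and evaluation (Table 4 footnote). It is not described as asking for the primary outcome.
- **Missing outcomes.** They are multiply imputed in the intention-to-treat analysis if MAR or missing completely at random holds (Sensitivity analysis and missing values).

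**The concern.** In two of the three trials the main question can be answered with one number, yet that number is requested only inside a long form that closes after eight weeks. The described safeguards miss the participant who simply does not answer. The logoff form needs active deregistration, and contact by telephone or e-mail is left to the participant. The stated response to high dropout is to recruit more people, which restores the number observed but does not reduce the missing share.

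Two features add to the burden on poor responders. The 19-item evaluation block is shown again to those who skipped it earlier. The voucher for completing the surveys requires all four questionnaires, so a participant who has missed one has no voucher left to earn at t3.

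At stake is how far the t3 comparison rests on MAR, which the observed data cannot verify. Participants who relapsed or regained weight may be less willing to report it, and in an unblinded comparison this may differ by arm.

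**Working it through.** **1. Items at t3** (rows marked at t3 in Tables 2 to 4, using the bracketed t3 counts where given)

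| Block | Weight | Fitness | Smoking |
|---|---|---|---|
| Sociodemographic (1+1+1+1+2+2) | 8 | 8 | 8 |
| Basic variables (6+1+1) | 8 | 8 | 8 |
| Outcomes | 90 | 119 | 50 |
| Confounders | 17 | 15 | 23 |
| Recommendation, text box | 2 | 2 | 2 |
| **Total** | **125** | **152** | **91** |
| With the repeated 19-item block | 144 | 171 | 110 |
| Primary outcome alone | 1 | 17 | 1 |

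Outcome rows, in table order:
- Weight: 1+17+1+7+18+2+32+12 = 90
- Fitness: 1+17+1+12+29+13+2+32+12 = 119
- Smoking: 1+1+1+9+18+2+6+12 = 50

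Confounders: Weight 3+14, Fitness 3+12, Smoking 3+3+17.

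**2. The plan's own sample size** (Table 5; two-sided alpha 0.05, power 0.80)

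- d = 0.25: a two-sample t test needs 252.1, so 253 per arm. 253/0.5 = 506; 1012 × 1.1 = 1113.2, so 1114.
- 15% versus 2%: 77 per arm is reproduced by Fisher's exact test (power 0.801). 77/0.5 = 154; 308 × 1.1 = 338.8, so 339.

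Both figures reproduce, and the 50% loss is built in.

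**3. Power at the planned N by share missing at t3**

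There are 1114/2 = 557 per arm (Fitness, Weight) and 339/2 = 169.5 (Smoking). With n observed per arm, power for means is Φ(d·√(n/2) − 1.96). For Smoking it is the pooled normal approximation. Only the 50% loss comes from the protocol.

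| Missing at t3 | n per arm, Fitness | Power, d = 0.25 | n per arm, Smoking | Power, 15% vs 2% |
|---|---|---|---|---|
| 60% | 222.8 | 0.75 | 67.8 | 0.78 |
| 50% | 278.5 | 0.84 | 84.75 | 0.87 |
| 45% | 306.4 | 0.87 | 93.2 | 0.90 |
| 35% | 362.1 | 0.92 | 110.2 | 0.94 |

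For Weight's own primary outcome (d = 0.50), power exceeds 0.999 at both 50% and 60% loss.

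**4. Effect of a short form.** Assume a share q = 10-30% of all t3 non-responders answers it. Missingness becomes 0.50 × (1 − q) = 45-35%, which gives the last two rows. From 60% loss it becomes 54-42%, with power 0.81-0.89 (Fitness) and 0.84-0.91 (Smoking).

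**5. Bias.** Let m be the missing share and g the gap between the responder mean and the non-responder mean in one arm. The responder-only mean is off by m·g.

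- If those recovered resemble the remaining non-responders, the error becomes m(1−q)·(1−m)/(1−m+mq)·g. With m = 0.5 it falls from 0.50g to 0.41g (q = 0.1) or 0.27g (q = 0.3).
- If those recovered resemble the responders, the observed mean does not move and the error is unchanged.

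**The case against.** **A reader might infer that all 91 to 152 items must be answered before the primary outcome counts.** The documents do not support this. The per-protocol definition lists taking part at all time points and filling in the primary outcome as separate conditions. The missing-data section foresees complete outcomes with missing predictors. What is established is narrower: the form must be returned within the window. Reminders, item order and saving of partial answers may be set out in the full protocol, and their absence from the article is not criticised here.

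**A reader might infer that the trials are underpowered or that silent non-responders are excluded.** Neither follows. Table 5 doubles n for 50% loss and adds a buffer, so power at 50% loss is above 0.80. Non-responders stay in the intention-to-treat set through imputation; what is missing is the observed value.

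**The power argument does not carry equally to all three trials.** This stands. The d = 0.25 gain belongs to Fitness, where the short form needs 17 items. Weight's own primary outcome has power to spare. A one-item weight form would also not recover the physical-activity outcome that set that trial's n.

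**The recovery rate has no basis in the documents.** This also stands. The protocol attributes dropout to low commitment, dissatisfaction, technical problems and the pandemic, not to form length, and those who deregistered may be unreachable. The planned mixed model also uses earlier time points, so the true power gain may be smaller than a t3-only calculation shows. Nor is a bias reduction proportional to the missing share assured (step 5).

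**Existing measures** (vouchers, t1 response monitoring, drop-out and per-protocol analyses) are real, but none yields a t3 primary outcome from someone who does not return the form.

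**Conclusion.** The concern holds as a worthwhile, inexpensive design improvement; the plan contains no error of calculation on this point. As described, a 1-item (Weight, Smoking) or 17-item (Fitness) primary outcome is reachable at t3 only through a form of about 125, 91 or 152 items. At the planned loss, about half of the t3 primary outcomes would be imputed under MAR.

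The main benefit is to replace some imputed values with observed ones and to protect against loss above 50%, which the protocol itself considers possible. With 10-30% recovery, Fitness power would rise from 0.84 to 0.87-0.92 and Smoking power from about 0.87 to 0.90-0.94. Weight would gain essentially no power, only less reliance on imputation. Bias shrinks only to the extent that those recovered resemble the remaining non-responders.

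These figures assume equal loss in both arms, an analysis of observed t3 values, and a recovery rate that the protocol does not give.

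**What to change.** In the last one to two weeks before a t3 questionnaire is blocked, send those who have not yet responded a form with the primary outcome only: current weight, 30-day abstinence, or the 17 BSA items. Use the existing survey platform. Count the answers as observed in the intention-to-treat analysis, flag them in the data set, and run one sensitivity analysis that leaves them out. State whether a short form counts as participation for the per-protocol set and as a completed questionnaire for the voucher.

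The cost is one extra survey link and e-mail. Short-form responders give no secondary outcomes, and a few people may prefer it to the long form; sending it late limits this. Timing matters too. Enrolment ran from 1 January to 5 October 2020, and t3 comes 12 months after a 6- or 12-week program, so if programs began soon after enrolment the earliest t3 windows closed in spring 2021, before the article appeared in August 2021. A form introduced after that point mixes two ways of ascertaining the outcome, and the report should give the start date and the number of short-form answers by arm.
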